## B. Bayesian data analysis

Fix any one of our dependent variables of interest  $y$  (e.g., permanent income). We estimate a multivariate linear regression model,  $y_i = \mathbf{x}_i' \boldsymbol{\beta} + \varepsilon_i$ , where  $i = 1, \dots, N$  indexes individuals,  $\varepsilon_i \sim_{\text{i.i.d.}} N(0, \eta^2)$ , with  $\eta^2$  known and  $\mathbf{x}_i$  fixed. Let  $x_{ij} \in \mathbf{x}_i$  be the key independent variable (either a self-control index or a measure of delay of gratification in childhood) and  $\beta_j$  be the corresponding coefficient in vector  $\boldsymbol{\beta}$ . We have a Gaussian prior on the population coefficient  $\beta_j \sim N(\theta, \nu^2)$ . Below, after deriving the posterior distribution for  $\beta_j$ , we discuss how we set values of  $\theta$  and  $\nu^2$ .

The OLS estimate for the coefficient vector is given by the usual formula  $\hat{\boldsymbol{\beta}} = (\mathbf{X}'\mathbf{X})^{-1}\mathbf{X}'\mathbf{y}$ , where  $\mathbf{y}$  and  $\mathbf{X}$  denote, respectively, the vector of observed values of the dependent variable and the matrix of observed values of the independent variables across the  $N$  individuals. Define the matrix  $\boldsymbol{\Sigma} \equiv \eta^2(\mathbf{X}'\mathbf{X})^{-1}$ . As is well known,  $\hat{\boldsymbol{\beta}}|\boldsymbol{\beta}, \boldsymbol{\Sigma} \sim N(\boldsymbol{\beta}, \boldsymbol{\Sigma})$ . Hence the conditional distribution of the  $j^{\text{th}}$  element of  $\hat{\boldsymbol{\beta}}$ , denoted  $\hat{\beta}_j$ , depends only on the  $j^{\text{th}}$  element of  $\boldsymbol{\beta}$ , denoted  $\beta_j$ , and the  $jj^{\text{th}}$  entry of  $\boldsymbol{\Sigma}$ , denoted  $\sigma_j^2$ . Specifically,  $\hat{\beta}_j|\beta_j, \sigma_j^2 \sim N(\beta_j, \sigma_j^2)$ . It follows that the vector  $(\hat{\beta}_j, \sigma_j^2)$  is a sufficient statistic for the posterior distribution of  $\beta_j$  (i.e., the posterior distribution of  $\beta_j$  depends on  $(\mathbf{y}, \mathbf{X})$  only through  $(\hat{\beta}_j, \sigma_j^2)$ ). We can therefore write the posterior distribution of  $\beta_j$  as  $f(\beta_j|\hat{\beta}_j, \sigma_j^2)$ , where we use  $f(\cdot)$  to denote a probability density function.

The prior for  $\beta_j$  is

$$f(\beta_j) = \frac{1}{\sqrt{2\pi\nu^2}} e^{-\frac{1}{2\nu^2}(\beta_j - \theta)^2},$$

and the likelihood of observing  $\hat{\beta}_j$ , given the true population  $\beta_j$  and the observed  $\mathbf{X}$ , is

$$f(\hat{\beta}_j|\beta_j, \sigma_j^2) = \frac{1}{\sqrt{2\pi\sigma_j^2}} e^{-\frac{1}{2\sigma_j^2}(\hat{\beta}_j - \beta_j)^2}.$$

Standard calculations yield the posterior distribution,

$$\beta_j|\hat{\beta}_j, \sigma_j^2 \sim N\left(\frac{\nu^2}{\sigma_j^2 + \nu^2} \hat{\beta}_j + \frac{\sigma_j^2}{\sigma_j^2 + \nu^2} \theta, \frac{\sigma_j^2 \nu^2}{\sigma_j^2 + \nu^2}\right).$$

In the last part of this section, we explain how we set the parameters of the prior distribution,  $\theta$  and  $\nu^2$ . Without loss of generality, orient all the dependent variables so that their expected correlation with the self-control independent variable is positive. Regarding  $\theta$ :

- When the independent variable  $x_{ij}$  is *deviation in delay time measured in the marshmallow task*, we set  $\theta$  such that the prior on the partial correlation between  $y_i$  and  $x_{ij}$  (controlling for the other independent variables in  $\mathbf{x}_i$ ) has mean 0.05.
- When the independent variable is a *multi-year self-control index*, we set  $\theta$  such that the prior on the partial correlation between  $y_i$  and  $x_{ij}$  has mean 0.15.

For all analyses, we will fix the standard deviation of the correlation at 0.2. See [subsection C](#) below for discussion of these prior distributions and related existing evidence.

We obtain the value of  $\theta$  from the assumed partial correlation as follows. The partial correlation between  $y_i$  and  $x_{ij}$  is equivalent to the coefficient from estimating the same regression using standardized dependent and independent variables (i.e., subtracting the mean and dividing by the standard deviation, so that each resulting standardized variable has mean 0 and variance 1). If we represent this corresponding model with standardized variables as  $\tilde{y}_i = \tilde{x}_i' \tilde{\beta} + \tilde{\varepsilon}_i$ , then as noted,  $\tilde{\beta}_j$  is equal to the partial correlation between  $y$  and  $x_j$  (hereafter we drop the  $i$  subscripts). Thus, our parameter of interest can be written

$\beta_j = \tilde{\beta}_j \left( \frac{SD_y}{SD_{x_j}} \right)$ , where  $SD_y$  and  $SD_{x_j}$  are the respective population standard deviations. We estimate these standard deviations using their sample counterparts.

We set  $\theta$  as the value of  $\beta_j$  that would correspond to the mean of our prior on the correlation. For example in an analysis with a multi-year self-control index as the independent variable, we would set

$\beta_j = 0.15 \left( \frac{SD_y}{SD_{x_j}} \right)$ , corresponding to a correlation of 0.15. Similarly, we set  $v^2 = \left( 0.2 \left( \frac{SD_y}{SD_{x_j}} \right) \right)^2$ . As noted above,  $v^2$  is held fixed when exploring the range of values for  $\theta$ .

## C. Discussion of priors for Bayesian analysis

### 1. Mean of the correlation between outcome measures and self-control measures

Recall that in our Bayesian data analysis (see [Section VI](#) and [Subsection B](#) above), we set the mean of our prior distribution such that it corresponds to a partial correlation between each outcome variable and the independent variable of...

- ...0.05 when the independent variable is *deviation in delay time measured in the marshmallow task*.
- ...0.15 when the independent variable is a *multi-year self-control index*.

For all three independent variables, we set the standard deviation of our prior distribution to correspond to a standard deviation of 0.20 for the partial correlation. In this section, we briefly discuss some of our reasoning and some of the related evidence that helped motivate these calibrations for the parameter values.

In the prior work most similar to our own, Moffitt et al (2011) explore correlations between a multi-year self-control index (a composite of behaviors measured from age 3 to 11) and several wealth outcomes measured at age 32. Controlling for gender, they find correlations with wealth outcomes are in the range of 0.15-0.27. Controlling for childhood socioeconomic status, IQ, and gender, they find correlations with wealth outcomes are in the range of 0.08-0.23. Moffitt et al use different measures of self-control and a different set of outcome variables so these findings are not fully analogous with our own analyses, but

their results provide a helpful point of reference and suggest that our prior mean 0.15 is perhaps slightly conservative.

In a meta-analysis, Richard, Bond, and Stokes-Zoota (2003, p.337) find that the average “person effect”—the estimated relationship between a social behavior and a demographic, personality, or other dispositional variable—across 16,282 estimated effects is 0.19. Compared to this benchmark, 0.15 again seems somewhat conservative.

For correlations between our outcomes and a measure of performance on the marshmallow delay task, we use as our benchmark prior an even lower correlation of 0.05. We hypothesize that behavior in the marshmallow delay task will have less explanatory power than the self-control indices as it is a single measure of self-control ability measured much earlier in life (and further from the outcomes) than the self-control indices.

## **2. Standard deviation of the correlation between outcome measures and self-control measures**

Finally, we discuss how we set the standard deviation for our prior. We note that, unlike for the mean where a value closer to zero is clearly more conservative, it is ambiguous whether a larger or smaller standard deviation is more conservative: a larger standard deviation means that the prior distribution has less overall impact on the conclusions relative to the data, but a smaller deviation shrinks large estimated effects more toward the (conservative) mean of the prior distribution. We think that a standard deviation of 0.20 roughly captures our degree of uncertainty about the strength of the correlation for both independent variables. For example, it means that our approximate 95% confidence interval (mean  $\pm$  2 standard deviations) on the correlation between the multi-year self-control index and an outcome variable is (-0.25, 0.55). (By way of comparison, Richard, Bond, and Stokes-Zoota (2003, p.336) find that about 5% of published findings in social psychology report correlation coefficients larger than 0.50.)

## **D. False discovery rate control**

Let  $H_{01}, H_{02}, \dots, H_{0N}$  denote  $N$  the null hypotheses we want to test. Suppose that of these hypotheses, the null hypothesis is actually true in  $N_0$  cases, and the non-null is true in  $N_1 (= N - N_0)$  cases. We want to adopt a decision rule, a rule that uses the  $p$ -values to declare  $R$  of the hypotheses as significant and  $N - R$  as non-significant (e.g., the Bonferroni decision rule would be: reject  $H_{0i}$  if  $p_i < 0.05/N$ ). Some of the hypotheses declared significant are actually null; let  $a$  denote the number of these. Some of the hypotheses declared significant are actually non-null; let  $b$  denote the number of these.

One approach to avoiding false positives is to adopt a decision rule that bounds the probability that *at least one* true null hypothesis is declared significant. This probability,  $\Pr(a > 0)$ , is called the family-wise error rate (FWER). The most well-known method of controlling the FWER is the Bonferroni decision rule. In our context, controlling the FWER would not be very informative because, given our relatively small sample size, our power to reject the family-wise null (that at least one of the null hypotheses is true) is very small.

The approach we focus on instead is to adopt a decision rule that bounds the (expected) proportion of true null hypotheses that are declared significant. This proportion,  $\frac{\alpha}{R}$ , is called the false discovery rate (FDR). Just as a rejection threshold must be chosen in classical testing for a single null hypothesis (conventionally 0.05), controlling the FDR requires specifying a FDR threshold  $q$  (conventionally 0.10).

The most widely known method of controlling the FDR is Benjamini and Hochberg's (1995) algorithm. It proceeds as follows. Compute a  $p$ -value for each  $i = 1, \dots, N$ . Re-index the  $p$ -values in increasing order:  $p_{(1)} \leq p_{(2)} \leq \dots \leq p_{(N)}$ . Find the largest index  $i_{max}$  such that

$$p_{(i)} \leq \frac{i}{N} q.$$

The decision rule, denoted  $BH(q)$ , is: declare all hypotheses  $i \leq i_{max}$  as significant and all hypotheses  $i > i_{max}$  as non-significant.

Benjamini and Hochberg (1995) proved that if  $p_1, \dots, p_N$  are mutually independent, then under  $BH(q)$ ,

$$E\left(\frac{\alpha}{R}\right) = \left(\frac{N_0}{N}\right) q \leq q.$$

In words, the expected proportion of false discoveries is at most  $q$ . In our application, because the life outcomes we study are correlated, the assumption of independent  $p$ -values across hypotheses almost surely does not hold. Below, we return to this point and explain why the decision rule  $BH(q)$  typically performs well even when the independence assumption does not hold.

To help clarify that point, and to aid in interpreting the decision rule  $BH(q)$ , note that  $BH(q)$  also has an empirical Bayes interpretation (Efron, Tibshirani, Storey, and Tusher, 2001). Let  $F(p)$  denote the true (unknown) cdf of the  $p$ -values, and  $F_0(p)$  denote the theoretical cdf of the  $p$ -values under the null hypothesis. Using Bayes' Rule,

$$\Pr(\text{hypothesis } (i) \text{ is actually null} \mid \text{its } p\text{-value} \leq p_{(i)}) = \frac{F_0(p_{(i)}) \Pr(\text{hypothesis } (i) \text{ is actually null})}{F(p_{(i)})}$$

Note that because each  $p_{(i)} \sim U(0,1)$ , we know that  $F_0(p_{(i)}) = p_{(i)}$ . We can estimate  $F(p)$  by its empirical counterpart,  $\bar{F}(p) \equiv \frac{\#\{p_i \leq p\}}{N}$ , and note that (due to the assumption of independence across hypotheses)  $\bar{F}(p_{(i)}) \equiv \frac{i}{N}$ . We can replace  $\Pr(\text{hypothesis } (i) \text{ is actually null})$  by its average value,  $\frac{N_0}{N}$ . Substituting,

$$\widehat{\Pr}(\text{hypothesis } (i) \text{ is actually null} \mid \text{its } p\text{-value} \leq p_{(i)}) = \left(\frac{N_0}{N}\right) \frac{p_{(i)}}{\left(\frac{i}{N}\right)}$$

If the threshold rule holds with equality at  $i_{max}$ ,  $p(i_{max}) = \frac{i_{max}}{N} q$ , then

$$\widehat{\Pr}(\text{hypothesis } (i_{max}) \text{ is actually null} \mid \text{its } p\text{-value} \leq p_{(i_{max})}) = \left(\frac{N_0}{N}\right) q \leq q.$$

All hypotheses  $i \leq i_{max}$  are weakly less likely than  $i_{max}$  to be null, given their  $p$ -values. Therefore, for all hypotheses with  $p_{(i)} \leq p_{(i_{max})}$ ,  $\widehat{\Pr}(\text{hypothesis } (i) \text{ is actually null} \mid p_{(i)} \leq p)$  is at most  $q$ . In words, under decision rule  $BH(q)$ , the probability that a hypothesis declared to be significant is actually null is at most  $q$ .

The empirical Bayes justification of the decision rule  $BH(q)$  makes it easier to see why the independence assumption is not crucial. In the empirical Bayes argument, the independence assumption is used only in making the claim that  $\bar{F}(p)$  is an unbiased estimate of  $F(p)$ . Efron (2010, Lemma 2.1 and p.55) shows that, in the absence of the independence assumption,  $\bar{F}(p)$  is biased upward—and hence the decision rule  $BH(q)$  is even more conservative. Moreover, Efron argues that in practice, the bias is small. The main cost of greater correlation in the  $p$ -values is that the estimated false discovery rate has greater sampling variation.

### **E. Multiple imputation of self-control scores for robustness checks**

As a robustness check, we plan to test the sensitivity of our results to the imputation method used for missing self-control scores in 1984, 1993, and 2003.

To calculate a measure of aggregate self-control, we would like to (1) normalize the self-control scores in each year (1984, 1993, and 2003) using the inverse-normal transformation, (2) average the three scores, and (3) re-normalize the final variable to get an aggregate measure of self-control as measured in 1984, 1993, and 2003. To handle missing data in this robustness check, we perform an additional step between steps 1 and 2 to impute missing self-control scores in each year. All imputation analyses are limited to the 110 subjects with a self-control score for at least one year.

As a robustness check, we use multiple imputation, a technique that incorporates random error into the imputed value to reflect uncertainty. The general idea of multiple imputation is to generate  $m > 1$  different imputed datasets, perform the analysis on each of the completed datasets (1 through  $m$ ), and pool the results of the individual analyses to get a single coefficient and standard error that simultaneously accounts for uncertainty in the coefficient estimates and uncertainty in the imputed values. Like other imputation methods, multiple imputation assumes that the data are missing at random conditional on observed variables, i.e., that the probability that the data are missing does not depend on unobserved variables.

There are different ways to draw the random error that enters into multiple imputation. We adopt one standard approach, in which it is assumed that the variables—those with missing values (the self-control measures) and those used to predict the variables with missing values—are drawn from a multivariate normal distribution. We view this approach as natural in our context because the inverse-normal transformation that we apply to many of the variables in our analysis ensures that their marginal distributions are normal.

A key modeling decision is which variables to include as predictors of the self-control measures. Best practice is to include *all* variables that play into the ultimate analyses of interest, including the dependent variables (von Hippel 2007). This is because excluding variables from the imputation that will be

included in analyses (such as the dependent variables) can lead to coefficient estimates that are biased toward 0. In our case, we specify a multivariate normal imputation model including the three self-control scores, deviation in delay time (both in log-seconds and seconds), gender, all primary outcome variables, and all secondary outcome variables with the exception of SAT scores. All variables are transformed using the inverse-normal transformation with the exception of gender. SAT scores are excluded from the imputation model because the small sample size ( $n = 31$ ) results in parameter estimates that do not converge; consequently, analyses of correlations between imputed self-control scores and SAT scores may be biased toward 0. We include gender in the model even though it is binary because the multivariate normal imputation procedure has proven to be robust to some types of non-normality, including the presence of binary covariates (e.g., Lee & Carlin 2010). We do not believe inclusion of gender greatly impacts the model, either by model fit or for the prediction of self-control scores.

In the remainder of this section, we describe the multiple imputation procedure in more detail. For a complete treatment, see Little and Rubin (2002) and the Stata Multiple Imputation Manual.

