## III. Primary analyses

- We will test, in separate regressions, the relationship between each of 11 primary outcomes and 2 primary measures of self-regulatory and delay ability for a total of 22 primary analyses
- We will control for gender in all analyses (note that we do not control for age at the time of the delay task because, in the delay time analyses where age would be relevant, the variable we use—deviation from expected delay time—already takes age into account)
- Each regression will be of the following form

$$y = \alpha + \beta_1 \times x + \beta_2 \times male$$

where  $y$  is one of the primary outcomes,  $x$  is one of the primary right hand side variables (deviation from predicted delay time or self-regulatory competence),  $male$  is a dummy for being male, and  $\alpha$  is a constant.  $\beta_1$  is the coefficient of interest

- In analyses with savings rate as the primary outcome measure, we will also include permanent income as an additional covariate

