### **IV. Secondary analyses**

#### **A. Secondary outcome variables**

- We will test each of the five components of the index of forward-looking behaviors variable as separate secondary left-hand-side variables. These include:
  - Diet, exercise, and BMI
  - Smoking and alcohol use
  - Preventative health and dental care
  - Agreement with statements about procrastination
  - Carefully consider future consequences of current financial decisions
- We will test savings rate as an outcome variable without controlling for permanent income as a secondary analysis of savings behavior
- Because of small sample size for these measures, we will test Quantitative and Verbal SAT scores as two secondary outcome variables
- We will test the education scale as described in Ayduk et al (2000) as an additional outcome variable
- We will test current emotional state and satisfaction with present relationship as an additional outcome variable. This is a secondary outcome as we consider it to be a noisy measure of emotional well-being and happiness in relationships that focuses on current emotional states and relationships rather than stable emotional and personality traits

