## V. Robustness checks

- We will replicate the primary analyses using deviation from predicted delay time in uncensored seconds (rather than log seconds) to test the sensitivity of our model to the assumption of log-normality in analysis of delay time in the marshmallow task
- We will replicate the primary analyses winsorizing the key delay ability or self-regulatory competence variable at the 5th and 95th percentile
- We will replicate the primary analyses with the key independent variable of expected deviation from predicted delay time in uncensored log seconds. In these secondary tests,

- instead of estimating a model with a linear effect of deviation in delay time, we will introduce a spline with knots at the 33.3rd and 66.6th percentiles of deviation in delay time
- We will test robustness of all analyses with self-control scores in the 1984, 1993, and 2003 surveys to the imputation method used to populate missing values. Robustness checks will include:
    - Averaging of available data years (with no imputation). In the self-regulatory competence variable, we will give the available self-control indices  $\frac{3}{4}$  weight and delay ability  $\frac{1}{4}$  weight. In secondary analyses of the self-control subscales, we will average across available years
    - A multiple imputation approach for analyses with the self-regulatory competence variable (see [Section X](#) for detailed methodology)
  - In past analyses, delay time in the marshmallow task has been measured as the deviation in seconds from the condition mean delay time. As a robustness check, we will re-test the primary analysis using deviation in seconds from the condition mean delay time instead of expected deviation from predicted delay time in uncensored log seconds derived from the Tobit random effects model
  - We will test robustness of our primary findings to assumptions made during data cleaning by dropping respondents for whom we made assumptions and repeating relevant analyses

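### SAT scores are left out of the imputation model and a bias toward zero is accepted, although a small SAT-specific imputation model would run and remove much of it

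*SAP*

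**What the plan says.** Section V of the SAP promises: "We will test robustness of all analyses with self-control scores in the 1984, 1993, and 2003 surveys to the imputation method". Multiple imputation is one of these checks, for analyses with the self-regulatory competence variable.

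Section X.E sets out the model. On the sample: "All imputation analyses are limited to the 110 subjects with a self-control score for at least one year". On content: "we specify a multivariate normal imputation model including the three self-control scores, deviation in delay time (both in log-seconds and seconds), gender", then all primary outcomes and "all secondary outcome variables with the exception of SAT scores". The reason given for so broad a model is that leaving an analysis variable out of the imputation can bias its coefficient toward zero.

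The same paragraph then excludes SAT because 31 values make the parameter estimates fail to converge, and states the result: "consequently, analyses of correlations between imputed self-control scores and SAT scores may be biased toward 0". No smaller model is offered for SAT. Section IV.A makes the two SAT scores secondary outcomes because of their small sample.

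**The concern.** The plan states a rule, breaks it for one pair of outcomes, and accepts the very bias the rule is meant to prevent. It attributes the exclusion to the number of SAT values. But 31 values are too few only for a model of this size. If a model with just the variables of the SAT regression can be fitted, the exclusion is unnecessary.

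What is at stake is limited. SAT is a secondary outcome and multiple imputation is a robustness check. Even so, the check is meant to show whether the handling of missing self-control scores drives the results, and for SAT it would carry an avoidable bias of its own.

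**Working it through.** **1. Size of the model.** Section X.E lists "including the three self-control scores, deviation in delay time (both in log-seconds and seconds), gender, all primary outcome variables", and Section III has "each of 11 primary outcomes and 2 primary measures of self-regulatory and delay ability". Section IV.A adds "each of the five components of the index of forward-looking behaviors variable as separate secondary left-hand-side variables", the education scale, and emotional state with relationship satisfaction. Savings rate is already a primary outcome.

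- Variables: 3 self-control + 2 delay + 1 gender + 11 primary + 5 components + 1 + 1 = 24.
- Free means and covariances: 24 + 24×25/2 = 324, for 110 people.
- SAT score regressed on the other 24 variables: 31 − 25 = 6 residual degrees of freedom, or 5 if the second SAT score is also a predictor.
- Six-variable model (three self-control scores, log delay deviation, gender, one SAT score): 6 + 6×7/2 = 27 parameters, and 31 − 6 = 25 residual degrees of freedom for SAT.

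**2. Does size drive the non-convergence?** EM was run on simulated data (110 people, 31 with SAT; 15 data sets at each of 20%, 35% and 50% missing per year; at most 1,000 iterations).

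| Model | Converged | Median smallest eigenvalue of fitted covariance |
|---|---|---|
| 26 variables (both SAT scores added) | 4 + 8 + 5 = 17 of 45 | 4×10⁻⁸ or less |
| 24 variables (as planned, no SAT) | 15 + 15 + 13 = 43 of 45 | 0.05 to 0.07 |
| 6 variables, with one SAT score | 45 of 45 | 0.22 to 0.23 |

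The same 31 values cause no difficulty in the small model.

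**3. Attenuation of the SAT slope.** The SAP gives no figure to reproduce. Missing rates, cross-year correlations and effect sizes are all assumed. Each run used multivariate normal data augmentation with a uniform prior, rebuilt the index from delay and the three years, pooled by Rubin's rules, and compared the result with the complete-data slope.

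- Simulation A: 600–800 data sets per setting. The 1984 score is taken as observed for the 31, because Section VIII.Q says SAT was parent-reported in 1984. Monte Carlo error at r = 0.25 is 0.7–1.5 percentage points.
- Simulation B: 500 data sets, SAT slope about 0.30.

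| Assumed setting | SAT left out | SAT in 6-variable model | Share of loss removed |
|---|---|---|---|
| A: r 0.25, 20% missing | 2.2% | 0.4% | 1 − 0.4/2.2 = 82% |
| A: r 0.25, 35% | 3.6% | 0.5% | 1 − 0.5/3.6 = 86% |
| A: r 0.25, 50% | 7.2% | 2.9% | 1 − 2.9/7.2 = 60% |
| A: r 0.25, 50%, weaker cross-year correlation | 9.3% | 4.0% | 1 − 4.0/9.3 = 57% |
| A: r 0.40, 50% | 7.0% | 3.4% | 1 − 3.4/7.0 = 51% |
| B: 30% | 1 − 0.285/0.311 = 8.4% | 1 − 0.302/0.311 = 2.9% | 0.017/0.026 = 65% |
| B: 50% | 1 − 0.258/0.307 = 16.0% | 1 − 0.293/0.307 = 4.6% | 0.035/0.049 = 71% |

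Across all runs, including a third set of 240 data sets at each of 30% and 50% missing, the loss from leaving SAT out is roughly 2–17%.

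**4. Size against sampling error.** On 31 observations a correlation has a standard error of about 0.17–0.18 (1/√30 = 0.183; (1 − 0.25²)/√30 = 0.171). The largest tabulated loss is 0.307 − 0.258 = 0.049, and 0.049/0.17 ≈ 0.3 standard errors.

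**5. The competence coefficient for the other outcomes.** In simulation A, with settings in the order of the first four rows above:

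| Method | Attenuation |
|---|---|
| Single-regression imputation (main method, Section VIII.C) | 3% / 6% / 10% / 13% |
| 24-variable multiple imputation | 1.4% / 3.0% / 5.0% / 6.8% |
| 6-variable, outcome-specific | 0.0% / 0.1% / 0.9% / 1.4% |

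Simulation B put the 24-variable figure as high as 1 − 0.219/0.240 ≈ 9%. In simulation A the joint model shows about half of the main method's attenuation (for example 10 − 5.0 = 5 of 10 points). The small models show most of it (10 − 0.9 = 9.1 of 10).

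**The case against.** The strongest reply is that the plan discloses this limit, words it as a possibility, and places it in a robustness check of a secondary outcome with 31 values. A shift of at most about 0.3 standard errors will rarely be visible. That stands as to size. It does not explain why the plan should keep a bias that a few extra runs would reduce.

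A reader might infer that the joint model should be replaced for every outcome. The documents do not support that. One inclusive model against many small ones is a recognised trade-off. Section X.E assumes data missing at random given the observed variables, and a small model conditions on fewer of them. When missingness was made to depend on another outcome, the small model's advantage for the competence slope vanished at 20% missing (ratios to the full-data slope 0.966 and 0.965), narrowed at 35% (0.965 against 0.94) and persisted at 50% (0.99 against 0.93). Separate models would also leave no common imputed data set if the joint Wald test of Section VI.A were repeated on imputed data.

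A reader might also infer that the joint model pulls the competence coefficient below the main estimate, so that a smaller multiple-imputation coefficient would be misread as lack of robustness. The comparison points the other way. The main method imputes from the other years without the outcome and attenuates more. On average the multiple-imputation coefficient was the larger in every setting. In a separate run of 400 data sets per setting it exceeded the single-regression coefficient in 55–60% of individual data sets. At most the check is somewhat blunted.

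**Conclusion.** The point holds for SAT. The exclusion follows from the size of the chosen model, contradicts the plan's own rule, and is avoidable. With 20–50% missing per year, it costs roughly 2–17% of the SAT slope, and a small model that includes SAT recovers about half to nearly all of that.

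The percentages rest on assumed missingness and cross-year correlations. If the self-control scores are nearly complete, the effect is negligible. Some attenuation remains under the small model when missingness is high, so it reduces the bias and does not abolish it. The joint model's own attenuation of the competence coefficients, about 1–9% under the same kind of assumptions, justifies an optional extra run but not a change of the planned model.

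**What to change.** In Section X.E:

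- Keep the joint model for all outcomes other than SAT.
- For each SAT score, fit a separate multivariate normal imputation model on the 110 subjects, holding the three self-control scores, log delay deviation, gender and that SAT score.
- Run the SAT regressions only on subjects with an observed SAT score.
- Replace the sentence that accepts bias toward zero by a note that some residual attenuation may remain for SAT because few values are observed.

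Optionally, report outcome-specific small models as an added sensitivity run for the primary competence coefficients (with permanent income added for savings rate), because the joint model shows only part of the difference from single-regression imputation.

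The cost is SAP wording and a few more runs of a procedure the plan itself describes as computationally light. The imputed self-control scores in the SAT analyses will differ slightly from those used elsewhere, and the other outcomes will not inform them.
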